#### Volunteer Support and Quality Assurance

Multiple systems are in place for volunteer support and quality assurance:

*Follow-up meetings:* The training team hosts weekly drop-in follow-up meetings for volunteers on Zoom^TM^. Trainers answer volunteers' inquiries and facilitate learning through group discussion and problem solving. Training and implementation can also be responsive to the emergent concerns and situations from these follow-up sessions. Although we encourage all volunteers to attend a follow-up meeting with the trainers, we emphasize to code red volunteers that they should refer to these sessions for extra support in managing their clients' cases.*Volunteer hotline:* Volunteers are provided with a phone number to call during working hours (9 a.m.−5 p.m., Monday through Friday) should they have clinical and/or urgent concerns regarding a client. An automatic system connects the volunteer with the clinician on-call for rapid assistance. The clinician support services are provided by professionals and advanced trainees with considerable experience in geriatric mental health (e.g., in the fields of geriatric psychiatry, clinical psychology and neuropsychology, occupational therapy, social work, and nursing).*Volunteer email address:* Volunteers are given an email address to contact in the case that (1) their client does not wish to receive the service anymore, (2) the volunteer would like to take on another client, or (3) the client/volunteer would like to be paired with someone new. A research assistant checks this email daily.*Client voicemail:* Upon entry into the telehealth intervention, a clinician provides clients with a voicemail number to contact should they have any queries (e.g., issues with their volunteer or the delivery of the service). The trainers instruct volunteers to additionally give this number to clients during their first contact. A team member checks this voicemail on a daily basis and relays the messages to the appropriate person. This voicemail is also used for clients who self-refer to receive TIP-OA.

### Interventional Methods

TIP-OA involves 1–2 times/week friendly phone calls from trained volunteers to adults >60 years old. Although the calls serve primarily to provide friendly conversation, they also grant volunteers the opportunity to inquire about clients' general well-being, provide information about COVID-19, and assess basic needs the client may have. If needed, volunteers refer clients to community resources and services (e.g., grocery or medication delivery, hotlines). In this way, the friendly phone calls may prevent against the worsening or development of mental health issues or may treat pre-existing or recent mental health conditions.

### Selection/Treatment of Subjects

The first 200 TIP-OA clients who provide informed consent will participate in data collection for research.

#### Exposure

The client exposure for the quantitative portion of this study is the TIP-OA intervention.

#### Client Quantitative Outcome Measures

All primary and secondary outcomes will be assessed over the phone at baseline, 4-, and 8-weeks (primary study endpoint):

##### Primary outcome

*The Perceived Stress Scale (PSS)* is a validated and commonly used measure of stress (28). The 14-item scale assesses the degree to which life events are appraised as stressful. It asks respondents about how often they have felt certain ways in the past month, with responses ranging from 0 (never) to 4 (very often).

##### Secondary outcomes

*The COVID Fear Scale* is an 18-item scale measuring individuals' anxiety, fear, and concern surrounding the COVID-19 pandemic. Items include: “Fear that I will be infected” and “Worry if I will be assigned to COVID wards if hospitalized” (29). The *Patient Health Questionnaire-9 (PHQ-9)* is a 9-item self-report questionnaire used to assess depressive symptom severity. The questionnaire asks individuals how often in the last 2 weeks they have been bothered by problems like “feeling down, depressed, and hopeless” and “poor appetite or overeating.” Scores for each question include 0 (not at all), 1 (several days), 2 (more than half of the days), and 3 (nearly every day) (30). The *Generalized Anxiety Disorder 7-Item Scale (GAD-7)* is a brief scale that measures symptoms of anxiety present in the previous 2 weeks. Respondents' scores can range from 0 (not at all sure) to 3 (nearly every day). Items include “Not being able to stop or control worrying” and “Being so restless that it's hard to sit still” (31). *Mental healthcare utilization* will be assessed using medical records, including the number of ER visits, hospitalizations, and outpatient visits (1) in the 8 weeks prior to baseline and (2) during 8-week follow-up.

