#### Client Referrals, Screening and Matching

Clients are either self-referred or referred from the JGH (COVID-19 inpatient units or the geriatric psychiatry clinic), long-term care facilities, local primary care clinics, or community organizations in the west-central Montreal healthcare/administrative catchment region (which represents over 500,000 residents from diverse ethnic backgrounds). Interested clients and clinicians can call our voicemail number, send an email, or fill out a form on our website to refer to our program. Included clients are consenting older adults (age ≥ 60) living in Montreal. Excluded individuals (1) are actively suicidal, (2) have a severe hearing impairment or other disability preventing the use of a phone, or (3) are suffering from moderate or severe dementia, as determined by clinical judgment (e.g., based on client history and/or past memory testing), or (4) are unable or unwilling to provide informed consent.

At intake, the screening clinician or trainee (e.g., in psychiatry, social work, psychology) spends 20–30 min on the phone with each client to collect basic demographic information and perform an informal clinical assessment regarding the client's level of cognitive functioning (coded as having suspected mild dementia or not). In cases where the client was referred from a clinic, our clinical team receives information from the referring clinician regarding the clients' cognitive and overall functioning. The screening clinician also assesses the client's level of risk and the complexity of their case, conducting a brief assessment developed primarily from Culo's paper (26) and national guidelines pertaining to seniors' mental health (27). This risk assessment is flexible and allows for the consideration of factors that are not included in the assessment, but that may hamper communication between the client and volunteer. The team then stratifies clients into categories based on case complexity and the initial risk assessment (Appendix B in Supplementary Material). Although we only assess case complexity at baseline, communication with volunteers through various channels (see section Volunteer Support and Quality Assurance) typically informs us of client mobility between categories. Following client screening and categorization, a clinician and volunteer manager assign clients to newly trained volunteers according to their assigned categories on a weekly basis.

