### Data Analysis

#### Quantitative Analysis

Descriptive statistics for continuous variables will include means and standard deviations, while categorical variables will be summarized using frequencies and proportions. A within-subjects repeated measure analysis of variance (ANOVA) will be conducted for the PSS (primary outcome), COVID Fear Scale, PHQ-9, GAD-7, and mental healthcare utilization (secondary outcomes) to assess differences in measures between baseline and the 8-week follow-up between groups with different baseline risk (low, medium, and high risk). Additional analysis of covariance (ANCOVAs) will control for variables that differ between groups at baseline. We will use LOCF to handle missing data that results from study attrition. Although we have found it extremely rare to be missing baseline data when, for example, a participant answers all but one question on a measure, in any such case we will exclude the participant's data for that measure. All ANOVAS will be tested at two-tailed alpha = 0.05. Linear mixed effect regression models, adjusting for age and sex, will analyze the effect of TIP-OA on all outcomes (PSS, COVID Fear Scale, PHQ-9, GAD-7, and mental healthcare utilization) collected at baseline and 8-week follow-up. We will perform additional linear mixed effect regression models accounting for a larger group of important variables such as client referral source (e.g., referred from clinic vs. self-referred) and cognitive functioning (e.g., suspected mild dementia vs. no suspected mild dementia) on mental health outcomes. Variable selection in linear mixed effect model (32) will be used to select important fixed effect covariates as they relate to the outcome. The fixed effect point estimates and corresponding confidence intervals and *p*-values will be computed. Additional subgroup analyses will also compare the primary outcome (PSS) between important subgroups [e.g., referral source (referred from clinic vs. self-referred) and cognitive functioning (suspected mild dementia vs. no suspected mild dementia)]. Analyses will be run using R statistical software.

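### Mental healthcare utilization is a raw visit count over two 8-week windows, with no allowance for follow-up time observed and an LOCF rule that does not suit such a count

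*Protocol article*

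**What the plan says.** All references are to the protocol article.

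- **Outcome and source.** Secondary outcomes gives the source of the utilization data: it "will be assessed using medical records". What is counted, and when, is set out there too: "including the number of ER visits, hospitalizations, and outpatient visits (1) in the 8 weeks prior to baseline and (2) during 8-week follow-up". The metric is a number of visits in each of two windows of equal nominal length.
- **Conflicting source.** Client Quantitative Outcome Measures says "All primary and secondary outcomes will be assessed over the phone at baseline, 4-, and 8-weeks (primary study endpoint"). Utilization is a secondary outcome, so the two sections disagree on its source. They also disagree on timing, because the definition has no 4-week count.
- **Analysis.** Under Quantitative Analysis, utilization goes into the same repeated-measures ANOVA as the questionnaire scales, "to assess differences in measures between baseline and the 8-week follow-up between groups with different baseline risk (low, medium, and high risk"). Then: "Linear mixed effect regression models, adjusting for age and sex, will analyze the effect of TIP-OA on all outcomes", and utilization is named among them. Neither model mentions time observed.
- **Attrition.** "We will use LOCF to handle missing data that results from study attrition". No outcome is exempted.
- **Population.** Clients are aged 60 or over. Some refer themselves or come from primary care or community organizations; others are "referred from the JGH (COVID-19 inpatient units or the geriatric psychiatry clinic), long-term care facilities".

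**The concern.** A questionnaire score is measured at a moment; a visit count builds up over time. Two counts can be compared directly only if both were collected over the same length of observation.

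That is not assured here. A client must be alive to enrol, so death cannot shorten the pre-baseline window. Death, a move out of reach of the records or withdrawal of record consent can shorten the follow-up window. Given the age range and some of the referral sources, such early ends are plausible.

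The plan handles utilization as if it were another scale score. Two things can then happen to a client who leaves:

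1. The record shows visits up to the leaving date and none after. Nothing marks the count as incomplete, so it is analysed as a full 8-week count.
2. The client is classed as lost to attrition and LOCF is applied. The definition gives only one earlier value, the pre-baseline count, so that is what is carried forward.

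Utilization is part of the first study objective, and the Abstract names lower healthcare use as a hoped-for benefit. The risk-group ANOVA also includes it, so early ends that differed between risk groups would distort that comparison as well.

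**Working it through.** The article states no attrition rate, visit rate or utilization effect, so there is no planned figure to reproduce. From the article come n = 200, two 8-week windows, and "All ANOVAS will be tested at two-tailed alpha = 0.05". Everything else below is assumed.

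**1. Partial counts entered as they stand.** Let *f* be the share of clients leaving early and *m* the mean share of the 8 weeks observed for them. With a constant visit rate that is the same on average in leavers and stayers:

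apparent change = −*f* × (1 − *m*)

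| *f* | *m* = 0.25 | *m* = 0.5 | *m* = 0.75 |
|---|---|---|---|
| 1% | −0.75% | −0.5% | −0.25% |
| 2% | −1.5% | −1.0% | −0.5% |
| 5% | −3.75% | −2.5% | −1.25% |
| 10% | −7.5% | −5.0% | −2.5% |
| 20% | −15.0% | −10.0% | −5.0% |

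If the leavers are heavier users the effect is larger. With 5% leaving halfway and using care at three times the rate of the others in both windows, their share of visits is 0.15 / (0.15 + 0.95) = 13.6%. Half of their follow-up visits are lost, giving a false fall of 6.8%.

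**2. Chance of a false significant fall.** This was simulated with 200 clients, no true change, gamma-Poisson counts (shape 0.7), uniform leaving times, a paired t-test (equivalent to a two-level repeated-measures ANOVA for the overall time effect) and 10,000 runs. The nominal rate for a fall is 2.5%.

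| *f* | raw, mean 0.5 visits | raw, mean 2 visits |
|---|---|---|
| 2% | 3.3% | 3.5% |
| 5% | 3.6% | 4.9% |
| 10% | 5.4% | 9.7% |
| 20% | 10.6% | 26.8% |

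The risk-group comparison was not simulated.

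**3. LOCF applied to leavers.** In the same simulation the mean change is between −0.2% and +0.2%, and the false-fall rate is 2.3% to 2.8%. The false fall disappears, but only because each leaver's change is set to zero. If LOCF is applied to a share *g* of clients and everyone's true change is Δ, the estimate is (1 − *g*) × Δ. At *g* = 10%, 90% of any true change, in either direction, remains.

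**4. One client, three treatments.** Take 4 visits in the 8 weeks before baseline (0.5 per week), the same rate afterwards, and departure at week 4.

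- Raw count: 0.5 × 4 = 2, change −2.
- LOCF: 4, change 0, whatever the client's real use.
- Rate over observed time: 2 / 4 × 8 = 4, change 0, taken from the client's own follow-up data.

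**5. Direction.** Even with raw counts, a leaver shows a fall only if the visit rate before leaving is below 1/*m* times the earlier rate: 4 times at *m* = 0.25, 2 times at *m* = 0.5, 1.33 times at *m* = 0.75. A steeper rise before death or institutional care would show as an increase.

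**The case against.** The strongest reply is that the plan does have an attrition rule, and under it a leaver shows no change rather than a fall. That is correct, and step 3 confirms it. A reader might infer from the unequal windows that use is bound to appear to fall, in the direction the study hopes for. The article does not support that: LOCF removes the fall, and use may rise before a client dies or moves. However, LOCF acts on values recognised as missing, and a records count that stops at week 3 need not look missing. Where LOCF is triggered, it discards counts that can still be read from the records.

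Secondly, the source is medical records, so stopping calls or interviews does not by itself end observation, and nothing in the article says extraction stops early. This stands, and it narrows the causes of truncation to death, moves and withdrawal of record consent. It also makes LOCF for a client who merely stops taking part harder to defend.

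Thirdly, extraction dates and partial windows are details a condensed article may leave to a fuller document. In part that is fair. But this article does fix the metric, the windows, the models and the attrition rule, and that combination does not suit the outcome.

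Two further inferences go too far. One is that every client was within reach of the records for all 8 earlier weeks. Only survival is assured, since no minimum period of residence is required. The other is that high-risk clients leave more often. Nothing shown links the risk code, used chiefly to match clients with volunteers, to death or relocation. An assumed 15% against 3% leaving halfway would give false falls of 7.5% and 1.5%, a gap of 6 percentage points, but that split is purely illustrative.

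**Conclusion.** The point holds as a mismatch between the outcome and its analysis, not as a demonstrated bias toward benefit. Survival is guaranteed in one window and not in the other, the models make no allowance for observed time, and the one attrition rule was written for scores rather than accrued counts. Depending on how the plan is applied, truncated counts pass as complete or recoverable counts are overwritten with pre-baseline values.

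The size is uncertain and probably modest. With raw counts, a constant rate and leavers observed for half the window on average, 5% leaving gives a false fall of 2.5% and 10% gives 5%. In the simulation, the chance of a false significant fall is at most 4.9% when 5% leave and reaches 5.4% to 9.7% when 10% leave. Under LOCF the distortion is toward no change. All of these rest on assumed leaving and visit rates. The outcome is secondary and the study has no control group, which limits the consequence, but the correction is cheap enough to make.

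**What to change.** 1. In the outcome definition, state that records are read through day 56 (8 × 7) for every consented client, whatever the status of calls or interviews, ending only at death, departure from the record area or withdrawal of record consent.
2. State that LOCF does not apply to utilization.
3. Record the days observed in each window and analyse visit rates in a count model with log observed time as an offset, in place of the ANOVA and linear mixed model on raw counts. Say that the result describes use while alive and under observation: the offset corrects for unequal time, not for a change in use shortly before death.
4. Report deaths and other early ends by risk group beside the utilization result.
5. Reconcile Client Quantitative Outcome Measures (all outcomes by phone, at three times) with Secondary outcomes (medical records, two windows).

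The cost is a few sentences, one extra variable for the last day observed, and slightly more analysis work in a records review already planned. No new contact with clients is needed.

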## Abstract

**Introduction:** Social-distancing due to COVID-19 has led to social isolation, stress, and mental health issues in older adults, while overwhelming healthcare systems worldwide. Telehealth involving phone calls by trained volunteers is understudied and may be a low-cost, scalable, and valuable preventive tool for mental health. In this context, from patient participatory volunteer initiatives, we have adapted and developed an innovative volunteer-based telehealth intervention program for older adults (TIP-OA).

**Methods and analysis:** To evaluate TIP-OA, we are conducting a mixed-methods longitudinal observational study.

**Participants:** TIP-OA clients are older adults (age ≥ 60) recruited in Montreal, Quebec.

**Intervention:** TIP-OA volunteers make weekly friendly phone calls to seniors to check in, form connections, provide information about COVID-19, and connect clients to community resources as needed.

**Measurements:** Perceived stress, fear surrounding COVID-19, depression, and anxiety will be assessed at baseline, and at 4- and 8-weeks. Semi-structured interviews and focus groups will be conducted to assess the experiences of clients, volunteers, and stakeholders.

**Results:** As of October 15th, 2020, 150 volunteers have been trained to provide TIP-OA to 305 older clients. We will consecutively select 200 clients receiving TIP-OA for quantitative data collection, plus 16 volunteers and 8 clinicians for focus groups, and 15 volunteers, 10 stakeholders, and 25 clients for semi-structured interviews.

**Discussion:** During COVID-19, healthcare professionals' decreased availability and increased needs related to geriatric mental health are expected. If successful and scalable, volunteer-based TIP-OA may help prevent and improve mental health concerns, improve community participation, and decrease healthcare utilization.

**Clinical Trial Registration**: ClinicalTrials.gov NCT04523610; https://clinicaltrials.gov/ct2/show/NCT04523610?term=NCT04523610&draw=2&rank=1

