The main limitation is that this study is non-blinded, non-randomized, and observational. If funding permits, we plan to conduct a pilot randomized controlled trial comparing outcomes of TIP-OA vs. a waitlist control. Another limitation is that our system for categorizing clients (Appendix B in Supplementary Material) is imperfect; although we based it off of previous literature and guidelines on geriatric mental health (26, 27) and it serves our purposes of facilitating appropriate matching between clients and volunteers, it does not account for the reality that people present with different types of risk. What's more, different risks may not map perfectly onto the categories that we developed. We were also not able to account for changes in risk category over the follow-up given that we only assessed client risk at baseline. It is possible that over the course of the 8 weeks, some clients moved between risk categories. Future research may consider using a universal, standardized risk assessment measure for coding clients' risk/case complexity at baseline and at the follow-up. Another potential weakness of this study is the lack of a structured cognitive assessment. We did not include a standardized measure as it would be challenging to administer over the phone with our limited human resources and time constraints. That said, our approach of documenting instances of clinician-suspected cognitive impairment is constructive in light of the aforementioned challenges, especially considering that several studies in the field of telehealth for geriatric mental health have not documented cognitive status in their reports (15, 47, 48).

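### The 8-week pre-baseline utilization window can contain the visit that led to a clinic referral, which biases the uncontrolled pre-post change toward an apparent fall

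*Protocol article*

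**What the plan says.** All places are in the protocol article.

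- **Outcome.** Under Secondary outcomes, mental healthcare utilization is taken from medical records, "including the number of ER visits, hospitalizations, and outpatient visits", counted "in the 8 weeks prior to baseline and (2) during 8-week follow-up". No rule is given for the contact that produced the referral.
- **Entry routes.** Under Client Referrals, Screening and Matching: "Clients are either self-referred or referred from the JGH (COVID-19 inpatient units or the geriatric psychiatry clinic", and the sentence goes on to long-term care, primary care clinics and community organizations. Self-referral is a working route; under Volunteer Support and Quality Assurance, "This voicemail is also used for clients who self-refer to receive TIP-OA".
- **Analysis.** Under Quantitative Analysis, linear mixed models adjusted for age and sex "will analyze the effect of TIP-OA on all outcomes", and utilization is on that list. Further models are planned, "accounting for a larger group of important variables such as client referral source (e.g., referred from clinic vs. self-referred". The subgroup comparison by referral source is stated for the PSS only.
- **Design and aim.** Strengths and Limitations says: "The main limitation is that this study is non-blinded, non-randomized, and observational". The Abstract hopes the program may "improve community participation, and decrease healthcare utilization", and effects on utilization belong to the first stated objective.

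**The concern.** A client referred at a clinic visit or from an inpatient unit is in the study because of that contact. The contact necessarily comes before baseline. If it falls within 8 weeks of baseline and counts as mental healthcare, it adds to the first count and nothing adds to the second. In a single-group study whose before-after change is read as the program's effect, the referral mechanism alone can then produce part or all of a fall.

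This is more specific than the general weakness of having no control group. The bias has a known direction, it favours the program, it bears on a stated objective, and it follows from the windows, entry routes and models that the article itself fixes.

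**Working it through.** **No figure to reproduce.** The Sample Size Justification gives no effect size, standard deviation, power or utilization rate. The share of clients referred from a clinic and the time from referral to baseline are not given either. What follows is a null model on stated assumptions.

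**Inputs from the article:** N = 200 (Selection/Treatment of Subjects); two-sided alpha 0.05 (stated for the ANOVAs, applied here to a paired comparison); two windows of 8 weeks; no control group.

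**Assumed inputs:**
- L = usual number of visits per 8 weeks, 0.25 to 2.
- g = share of all clients whose pre-window holds one referring visit *in addition to* their usual rate, 0 to 0.5.

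**Model with no program effect:** follow-up count ~ Poisson(L); pre-baseline count ~ Poisson(L) + Bernoulli(g).

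- Expected change per client = −g
- Apparent relative fall = g/(L + g)
- SD of the within-client difference = √(2L + g(1 − g))
- Chance of a significant false fall = Φ(g√N/SD − 1.96)

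*Example, L = 1 and g = 0.10.* SD = √(2 + 0.09) = 1.446. Standard error = 1.446/√200 = 0.102. Then 0.10/0.102 = 0.98, and Φ(0.98 − 1.96) = 0.163. The apparent fall is 0.10/1.10 = 9%.

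Chance of a significant false fall, with the apparent fall in brackets:

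| g | L = 0.25 | L = 0.5 | L = 1 | L = 2 |
|---|---|---|---|---|
| 0 | 2.5% (0%) | 2.5% (0%) | 2.5% (0%) | 2.5% (0%) |
| 0.05 | 16% (17%) | 10% (9%) | 7% (5%) | 5% (2%) |
| 0.10 | 45% (29%) | 27% (17%) | 16% (9%) | 10% (5%) |
| 0.25 | 99% (50%) | 90% (33%) | 67% (20%) | 41% (11%) |
| 0.50 | 100% (67%) | 100% (50%) | 99.7% (33%) | 93% (20%) |

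A simulation of 20,000 studies per cell agreed with these probabilities to within 0.5 percentage points.

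**Does adjusting for referral source help?** Each client contributes one value to each period, so referral source is balanced across periods. A main effect of source moves both periods equally and leaves the period effect where it was. A second simulation (200 runs, N = 200, L = 0.5, half the clients clinic-referred and each carrying one extra visit) gave these average estimates:

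- period effect without source: −0.50
- period effect with source as a main effect: −0.50
- with a source-by-period term: about 0.00 in clients without a referring visit, and about −1.00 in clients with one.

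Only the interaction shows where the fall comes from.

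**The case against.** The case on the other side is substantial and limits the claim.

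1. **The outcome is mental healthcare utilization.** A geriatric psychiatry visit clearly qualifies. A COVID-19 admission or a general primary care visit may not, and the article does not say.
2. **Not every client has a referring visit.** Self-referred and community-organization clients have none, and a clinician may refer by phone, email or web form without a fresh visit.
3. **Timing is unknown.** By 15 October 2020 there were already 305 clients, while recruitment of the 200 still lay ahead (Results—Early Experience). Some referring contacts may predate the window.
4. **A referring visit may be a routine one.** Suppose visits every 4 weeks and baseline d weeks after the referring visit, 0 < d < 4. The pre-window holds visits at −d and −(4 + d), the follow-up window visits at 4 − d and 8 − d: two each, and no bias. Deleting the referring visit leaves one against two, a spurious rise.
5. **Other forces act.** The program links clients to services, which could raise use. The article words its hope conditionally and names the observational design as its main limitation.

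All five stand as limits. A reader might infer that the window always contains the referring contact, that utilization must fall even if the program does nothing, or that a false positive is close to certain. The article supports none of these, because the affected share, the timing and the visits that count are not given. Nor does it support reading every clinic referral as an extra visit.

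These points do not remove the direction of the bias. Any client with an extra referring visit that counts pushes the change downward, and neither the main-effect adjustment nor the limitations text deals with that.

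**Conclusion.** The concern holds in a limited form. For clients referred from a hospital or clinic, the pre-baseline window can contain the contact that led to referral, and the uncontrolled change in mental healthcare utilization is biased toward an apparent fall.

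The amount cannot be computed from the article. The range of 10% to 45% for a false significant fall at g = 0.10, and 41% to 99% at g = 0.25, rests on assumed visit rates of 0.25 to 2 per 8 weeks, Poisson variation and a paired test on 200 clients. At g = 0.05 it is 5% to 16%; at g = 0 it is the nominal 2.5%. A modest share of affected clients is enough to matter, but that share is unknown.

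The planned referral-source covariate does not repair this, and the source subgroup analysis does not reach utilization. One secondary outcome is at stake. The PSS is not affected by this counting problem, nor are the other questionnaire scores.

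**What to change.** In Quantitative Analysis:

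1. Add a referral-source-by-period term to the utilization model, and report the pre-post change separately for self-referred and clinic-referred clients. State in which group long-term-care and community-organization referrals fall.
2. Add a sensitivity analysis that leaves the referring contact out of the pre-baseline count. Say that it can over-correct for clients on regularly scheduled visits; for that reason it should not replace the main count.
3. State that a fall confined to clinic-referred clients will not be attributed to TIP-OA. Barring every utilization claim unless self-referred clients also show a fall would be a matter of preference and is not needed here.

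The cost is small. Referral source is already to be used as a covariate. The sensitivity analysis needs the date of the referring contact, and whether it counts as mental healthcare, from medical records already being used. The downside is a less precise, and possibly less favourable, result on a secondary outcome.
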